#### Clinical Assessment

CHR is assessed using the SIPS, with symptom ratings measured via the Scale of Prodromal Symptoms (SOPS) (1). To assure reliable diagnostic and clinical assessment across sites, a consensus diagnosis procedure was developed, including weekly clinical calls with certified Ph.D. or M.D. raters, all of whom were trained by Yale developers of the SIPS. Participants are also administered Structured Clinical Interview for DSM-IV Axis I Disorders (SCID) (52). Current and past psychosocial treatment, medication and hospitalization data are collected for all participants. Finally, the Alcohol/Drug Use Scale (AUS/DUS) is administered to measure current substance use (53).

During the final group session, all participants are given an exit interview in which they complete a small survey examining overall satisfaction with the intervention. Participants are asked to provide self-rated impressions of improvement in concentration, memory, attention, as well as conversational and task vigilance. These impressions are rated on a scale of 1 (not at all helpful) to 10 (very helpful) referring to whether participants found the skills taught during group to be helpful in improving each respective domain of cognition. Participants are also given the opportunity to provide qualitative feedback regarding additional topics to be covered, topics to be removed, and feedback regarding difficulty attending group sessions, as well as any other suggestions to improve groups.

### Design Considerations

Focusing on compensatory and environmental strategies, rather than drill and practice computer exercises, is consistent with empirical focus on improving functional skills among patients with schizophrenia (54, 55). In addition to attention, learning and memory, and executive functioning, the CCT intervention targets prospective memory ability (i.e., the ability to remember to do things in the future, such as complete homework assignments or attend a doctor’s appointment). These CCT-targeted areas of cognition represent potentially modifiable cognitive domains with relevance for psychosocial functioning (27, 56, 57). Moreover, these domains represent areas of cognition also affected in the prodromal phase (9, 58) and predictive of later conversion to psychosis, thereby serving as key initial treatment targets. Prevention of further deterioration and preservation of cognitive abilities may be vital first steps to increase the effectiveness of other psychosocial treatments. Another strength of CCT is its exploitation of stronger cognitive functions in schizophrenia, such as imagery (59) and habit learning (60, 61), to bolster impaired abilities; for example, forming new habits in attention and problem-solving can lead to gains in performance efficiency *via* automatic processing and decreased cognitive demands. Increasing individuals’ ability to remember appointments, sustain attention, encode important concepts, and think flexibly may well improve the success of concomitant treatments.

### Therapist Training

Mental health providers at the bachelor’s level or above deliver the treatment. Two San Diego site therapists, as well as one investigator and one study therapist at the Mexico City site, were formally trained on the CCT protocol by [name] at study initiation. The 2-day training included an introduction to the theoretical principles underpinning the treatment model, specific instructions on implementing each of the twelve CCT sessions, and review of RT sessions. Weekly individual supervision is ongoing throughout the trial between the study therapists and PIs.

### Fidelity

Research recommendations by Perepletchikova and Kazdin (62) were implemented to maximize treatment manual adherence (e.g., use of checklists). All CCT and RT sessions are recorded to monitor fidelity; sessions are rated using items from the Cognitive Training Fidelity Scale (unpublished; available upon request from the authors). Therapist compliance was defined as 90% adherence to the items on the weekly checklist; subthreshold fidelity ratings will result in remedial training until these levels are achieved. To reduce the risk of treatment contamination, groups will be held at times and locations where subjects in different groups will not have the opportunity to meet in a waiting room. We will also ask subjects not to discuss their treatment with other subjects until after completion of the protocol. Monthly fidelity ratings will be fed back to therapists during supervision to improve fidelity. RT sessions will also be rated to ensure that RT groups do not receive training in CCT skills.

### Data Analysis

The purpose of this pilot RCT is to examine feasibility and generate effect sizes to establish benchmarks for future studies, not to complete an adequately powered efficacy study. Power calculations based on Cohen method (63) and the method provided by Hedeker et al. for the Random Regression Model (64) indicated that with the proposed sample size, we will have a minimum 80% power to detect a medium to large effect across groups, consistent with the medium to large effects in prior studies.

A linear mixed model, with post-hoc procedures if indicated, will be used to analyze data in order to compare CCT versus RT in Latino CHR subjects in the United States and Mexico (co-primary outcomes: neurocognition [Global Cognitive Index and individual domain scores] and functional capacity; secondary outcomes: self-reported functioning and clinical symptom severity). Feasibility data such as recruitment rate, consent rate, reasons for not participating, reasons for dropping out, participants’ satisfaction, and their suggestions to improve the study will be tabulated and will be analyzed descriptively.

Furthermore, predictors (moderators) of response to CCT versus RT, including age, baseline symptom severity, neurocognition, and comorbidity, will be explored. Moderators will be examined by building hierarchical linear models with potential moderator variables (e.g., baseline symptoms, neurocognition, functioning, age, and comorbidity) included in the model (65). The linear model to be used for both moderator and mediator analyses will compare CCT versus RT treatment groups. The independent variables are treatment group, moderator, and the treatment-moderator interaction. An interactive effect will mean that the effect of treatment on individual subjects depends on their value of moderator.

Finally, mediators of functional outcomes, including improvement in cognition and symptom severity, will be explored. Mediation analyses will use a similar linear mixed models approach. Two conditions must be met for mediation of the treatment effect: 1) correlation between the mediator and treatment; and 2) relationship between the mediator and outcome (65). First, we will test the effect of treatment group and the group × time interaction on the mediator (for example, improvement in cognition), and we expect a statistically significant group × time interaction. Second, we will test the effects of neurocognitive change (change score from baseline to mid-treatment) and the Global Cognitive Index change × group interaction on the outcome (UPSA) in the model that includes group and time, and we expect a statistically significant mediator × time or mediator × group × time interaction. The Global Cognitive Index change score from baseline to midway establishes temporal precedence of the mediator. We will also explore whether change in Global Cognitive Index and other variables mediates change in the other outcome variables (e.g., functioning). Finally, we will explore the relationships between specific measures (e.g., specific symptom factors) and functioning, number of sessions attended, as well as relationships between change in one domain and change in another (e.g., between change in symptoms, neurocognition, with change in functioning), when appropriate.

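### The exploratory mediation rule accepts either of two interactions, in either direction, so a pattern that contradicts the hypothesised mechanism can be labelled mediation (minor)

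*Protocol article*

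**What the plan says.** The Data Analysis section introduces the analysis as exploratory: "mediators of functional outcomes, including improvement in cognition and symptom severity, will be explored". It then sets requirements: "Two conditions must be met for mediation of the treatment effect". The first is that treatment and mediator are related. The second is a "relationship between the mediator and outcome".

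Each condition is tied to a test. For the first, on the mediator, "we expect a statistically significant group × time interaction". For the second, the article names the effects of cognitive change and the "Global Cognitive Index change × group interaction on the outcome (UPSA) in the model that includes group and time", and then states what is to be seen: "we expect a statistically significant mediator × time or mediator × group × time interaction".

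No significance level, direction or division of alpha is given for the two interactions. The same section says that the pilot is meant to "generate effect sizes to establish benchmarks for future studies" and is not adequately powered for efficacy.

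**The concern.** Three features of the second condition work together.

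- Either of two tests will do, so there are two chances of a false positive at that step.
- Neither test has a required sign. A significant mediator × time term may mean that participants whose cognition improved did worse on the UPSA.
- A significant mediator × group × time term shows only that the mediator-outcome slope differs between arms. It can arise when the slope in the CCT arm is zero or negative, which is not mediation of a CCT benefit.

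At stake is the mechanism claim that cognitive gain drives functional gain. It could be made from a chance interaction or from data that point the other way, and then carried into a larger trial. No primary or secondary treatment comparison is affected.

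**Working it through.** **Inputs.** From the article: 120 participants (Participants section) and the two conditions above. Assumed, because the article does not state them: 60 per arm, two-sided 0.05 per test, a CCT effect on the mediator of 0.5 or 0.8 SD, mediator-outcome slopes of size 0.3, unit SDs, one UPSA change per person, and no clustering or dropout.

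**Plan's own figure.** None is given for mediation. The only related figure is at least 80% power for a medium to large effect. With 60 per arm, the effect detectable at 80% power is (1.96 + 0.842) × √(2/60) = 0.51 SD. Power is 78% at 0.5 SD and 99% at 0.8 SD. The same two values give the chance of passing the first mediation step.

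**Model.** UPSA change is regressed on group, mediator and mediator × group. For a single change score, the mediator term stands for mediator × time and the product term for mediator × group × time. The result depends on how group is coded, which the article leaves open, so both codings are shown.

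**Step 2 alone, no mediator-outcome relation.**
- Centred coding (tests nearly independent): 1 − 0.95² = 0.0975, or 1.95 times 0.05.
- 0/1 coding: the mediator term is the RT slope (variance v) and the product term is the difference in slopes (variance 2v, covariance −v). Their correlation is −1/√2 = −0.71. The chance that at least one is significant is 0.083, or 1.66 times 0.05.

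**Both steps, no mediator-outcome relation.** The rate is roughly P(step 1) × P(step 2).

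| CCT effect on mediator | P(step 1) | Product, either/or rule | Simulated, either/or rule | Product, single step 2 test |
|---|---|---|---|---|
| none | 0.05 | 0.4-0.5% | 0.4% | 0.25% |
| 0.5 SD | 0.78 | 6.5-7.6% | 6.1-7.2% | 3.9% |
| 0.8 SD | 0.99 | 8.2-9.7% | 7.8-10.0% | 5.0% |

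In each range the lower figure is 0/1 coding and the upper is centred coding. The simulations used 8,000 trials per scenario.

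**Wrong direction: slope −0.3 in both arms.**
- 0/1 coding: the RT slope has standard error about 1/√60 = 0.129, so z = 0.3/0.129 = 2.32 and power is Φ(2.32 − 1.96) = 0.64. Times 0.78, this is 0.50.
- Centred coding: the averaged slope has standard error about 1/√120 = 0.091, so z = 3.29 and power is Φ(3.29 − 1.96) = 0.91. Times 0.78, this is 0.71.
- Simulation agrees: about 50-70% at 0.5 SD, and 63-89% at 0.8 SD.
- A true common slope of +0.3 gives the same range, about 50-69% at 0.5 SD. The rule therefore cannot tell the hypothesised mechanism from its opposite.

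**Opposite slopes: +0.3 in one arm, −0.3 in the other.** The difference of 0.6 has standard error about √(2/60) = 0.183, so z = 3.29 and power is about 0.91. Times 0.78, this is 0.71. Simulation gives 69-70% at 0.5 SD and 88-89% at 0.8 SD. The arm-averaged mediator term alone would be declared in only 4-5%.

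**The case against.** **The error rate.** A reader might infer that the false-positive rate for mediation nearly doubles to about 10%. That is true of step 2 only. Both conditions are required, so the rate for the whole rule is about 0.5% if CCT leaves the mediator unchanged and 6-8% at 0.5 SD. It approaches 10% only when the first step is almost certain to pass. The rule roughly doubles a single-test version (1.7 to 1.95 times, depending on coding), but that version is itself at or below 5%. This objection stands.

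**Opposite slopes.** A reader might also infer that mediation is declared where none exists. With opposite slopes each arm has a non-zero indirect effect, and the two cancel on average. The fault is the bare label, with no arm or sign attached.

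**Power.** It is tempting to say that the rule hides true mediation. With a common slope of +0.3 and centred coding it finds mediation about as often as an interval for the indirect effect would (69-70% for both). Only 0/1 coding loses power (50%), and the article does not prescribe that coding.

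**Status and omission.** The analysis is exploratory and phrased as an expectation. An indirect-effect estimate may sit in a fuller document, so its absence from an article is not a finding. The mediator is described as improvement in cognition and the trial hypothesis is directional, so a careful analyst would look at the sign. All this lowers the severity. It does not remove the point, because the article states requirements for mediation and the interactions expected to show the second, and what it states has no sign.

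**Cause of the sign problem.** The either/or is not its only source. A single two-sided test of the averaged term would also declare mediation in 88% of wrong-direction trials at 0.8 SD. Removing the either/or without stating a direction would not be enough.

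**Conclusion.** The point holds as a minor one about an exploratory analysis. The second mediation condition is met by either of two interactions in either direction. The either/or raises the rate of chance declarations modestly, to 6-8% for the full rule at 0.5 SD and 8-10% at 0.8 SD. The lack of a sign is the larger fault: with a 0.5 SD effect on the mediator, a wrong-direction relation is called mediation in about 50-70% of trials, and opposite slopes in about 70%.

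The sizes rest on the assumed 0.05 level, 1:1 allocation, slopes of 0.3 and no clustering. The absence of a sign rests on the article's text alone. The documents do not support any claim that the primary conclusions are at risk, or that the plan forbids reporting an indirect effect.

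**What to change.** Replace the either/or significance rule with one named quantity: the indirect effect of CCT on UPSA change through the mediator (the CCT effect on the mediator times the mediator-outcome slope). State its expected sign. Report it with a 95% confidence interval that respects the randomised therapy groups, for example a bootstrap that resamples groups. With 4-6 participants per group there would be about 120/6 = 20 to 120/4 = 30 groups, so that interval is itself approximate.

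Report mediator × group × time separately, as a check on whether the slope differs by arm. If it does, give the indirect effect by arm. Do not count that interaction alone as evidence that a CCT benefit is mediated.

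The cost is analysis wording and a short programme. The change itself calls for no new data, and it serves the stated aim of generating effect sizes. The downside is a little more analysis work and fewer mediation claims.

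One separate matter comes first. The mediator is defined as Global Cognitive Index change from baseline to mid-treatment, but Table 1 schedules the neurocognitive battery only at baseline, week 12 and week 24. Those passages must be reconciled; this fix does not resolve them.

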## Abstract

**Background:** Early psychosocial interventions targeting cognitive and functional outcomes in individuals at clinical high risk for psychosis are a research priority. An even greater need is the identification of effective interventions in underserved populations. Compensatory Cognitive Training (CCT) is a psychosocial intervention with demonstrated efficacy in chronic schizophrenia and first episode psychosis, but remains to be evaluated in pre-illness phases. The aim of this study was to describe the development and implementation of an ongoing pilot randomized controlled trial investigating the efficacy of group-based, manualized CCT, as compared to recreational therapy (RT), for Latino participants at clinical high risk for psychosis (CHR) in both the United States and Mexico. It is hypothesized that, in comparison to those receiving RT, participants receiving CCT will show significant improvements in neurocognitive performance and functional capacity (co-primary outcomes) and self-rated functioning and clinical symptoms (secondary outcomes).

**Methods:** Latino CHR participants aged 12–30 years will be included in the study. Both CCT and RT will be delivered in either Spanish or English, depending on group preference. Additionally, all assessments will be administered in participants’ preferred language. A comprehensive assessment of neurocognitive and functional performance and clinical symptomatology will be performed at baseline, mid-intervention (4 weeks, 8 weeks), post-intervention (12 weeks) and 3-month follow-up. The primary outcome measures are neurocognition and functional capacity, as assessed by the MATRICS (Measurement and Treatment Research in Cognition in Schizophrenia) Consensus Cognitive Battery and the University of California, San Diego Performance-Based Skills Assessment-Brief, respectively. Furthermore, secondary outcomes measures will be used to examine change in clinical symptoms and self-reported functioning in response to CCT versus RT.

**Discussion:** The evaluation of a novel treatment such as CCT in CHR youth will provide empirical support for a low risk, comprehensive cognitive intervention that could have important implications for public health if it improves neurocognition and functioning.

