### Assessments

Following enrollment/randomization, participants complete assessments at baseline, mid-intervention (4 weeks, 8 weeks), post-intervention (12 weeks) and 3-month follow-up, conducted by clinical raters and research assistants blind to group assignment (see **Table 1** for the Assessment Overview). Participants are compensated for their time per assessment and at each group session to offset the cost of transportation. Following baseline assessment, participants receive 12 weeks of their assigned intervention, delivered by bachelor’s level or above therapists at each site. Therapists administer both treatments in an alternating schedule to avoid therapist effects in the design. The primary outcome measures are neurocognition and functional capacity, as assessed by the measures detailed below. Furthermore, secondary outcomes measures will be used to examine change in clinical symptoms and self-reported functioning in response to CCT versus RT.

**Table 1 T1:** Assessment Overview.

	Time (Hour : Min)	Baseline	Week 4	Week 8	Week 12	Week 24
**Clinical (Day 1)**	**2:30**	**X**			**X**	**X**
Demographics	:15	**X**			**X**	**X**
SCID-I	1:00	**X**			**X**	**X**
SIPS/SOPS	1:00	**X**	**X**	**X**	**X**	**X**
AUS/DUS	:15	**X**	**X**	**X**	**X**	**X**
**Functional (Day 1)**	**1:35**	**X**			**X**	**X**
SAS-SR	:15	**X**			**X**	**X**
GAF	:05	**X**			**X**	**X**
SLoF	:30	**X**			**X**	**X**
UPSA	:45	**X**			**X**	**X**
***Day 1 Total***	***4:05***	**X**			**X**	**X**

**Neurocognitive** **Battery (Day 2)**	**2:15**	**X**			**X**	**X**

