**Executive Functioning**						
NAB Mazes	:10	**X**			**X**	**X**
WCST	:10	**X**			**X**	**X**
***Day 2 Total***	***2:15***	**X**			**X**	**X**

***Exit Interview***	***:30***				**X**	
**Total Assessment Time** (H:M)		**6:20**	**1:15**	**1:15**	**6:50**	**6:20**

Structured Interview for Prodromal Syndromes (SIPS), Scale of Prodromal Symptoms (SOPS), Structured Clinical Interview for DSM-IV (SCID) Axis I, The Social Adjustment Scale – Self-Report (SAS-SR), Global Assessment of Functioning (GAF), Specific Level of Functioning (SLoF), The UCSD Performance-Based Skills Assessment (UPSA), Wechsler Adult Intelligence Scale (WAIS), Hopkins Verbal Learning Test (HVLT), Brief Visual Memory Test–R (BVMT), Brief Assessment of Cognition in Schizophrenia (BACS), Category Fluency, Trail Making Part A, Continuous Performance Task Identical Pairs (CPT-IP), Wechsler Memory Scale (WMS), Univ. of Maryland Letter-Number Span (LNS), Neuropsychological Assessment Battery (NAB) Mazes, Wisconsin Card Sorting Test (WCST).

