#### Cognitive and Functional Assessment

Premorbid intellectual functioning is assessed *via* the Wechsler Adult Intelligence Scale (WAIS), Block Design and Vocabulary subtests. Participants are administered an expanded MATRICS (Measurement and Treatment Research in Cognition in Schizophrenia) Consensus Cognitive Battery (MCCB) in English or Spanish (47). The MCCB has excellent qualities, including psychometric properties for longitudinal studies, utility as a repeated measure, relevance to functional outcome, brevity, ease of use, and participant tolerability. These tests are administered according to published standardized procedures. As part of collaborative studies, the UCSD team has traveled to Mexico City and standardized administration of the neuropsychological battery. The battery includes the following domains: 1) Estimated IQ: Wechsler Adult Intelligence Scale Vocabulary and Block Design, 2) Learning & Memory: Hopkins Verbal Learning Test, Brief Visual Memory Test–R, 3) Processing Speed: Brief Assessment of Cognition in Schizophrenia: Symbol Coding, Category Fluency, Trail Making Part A, 4) Attention/Vigilance: Continuous Performance Task Identical Pairs, 5) Working Memory: WMS III Spatial Span, University of Maryland Letter-Number Span, and 6) Executive Functioning: Neuropsychological Assessment Battery Mazes, Wisconsin Card Sorting Test. A Global Cognitive Index will combine z scores of all cognitive domains per established methods (8). The University of California, San Diego Performance-Based Skills Assessment-Brief (UPSA-Brief) was selected to measure performance-based functional capacity (48), along with UPSA-Child and Adolescent version for adolescents. The Specific Levels of Functioning (SLOF) scale is used as a self-reported functioning measure because of its concordance with objective ability measures (49). In addition, the modified Global Assessment of Functioning (50) and the Social Adjustment Scale (51) are administered.

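### The exploratory cognitive mediation analysis needs a mid-treatment Global Cognitive Index that Table 1 does not schedule, and the abstract contradicts Table 1 on this

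*Protocol article*

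**What the plan says.** In the Data Analysis section, the second step of the mediation analysis uses "neurocognitive change (change score from baseline to mid-treatment" as the mediator and the UPSA as the outcome. The section then gives the reason for that timing: "The Global Cognitive Index change score from baseline to midway establishes temporal precedence of the mediator".

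Three other places bear on whether this mediator exists:

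- **What mid-treatment means.** The Assessments section states that "participants complete assessments at baseline, mid-intervention (4 weeks, 8 weeks), post-intervention (12 weeks) and 3-month follow-up". Mid-treatment is therefore week 4 or week 8. This sentence does not say which instruments are used at which visit.
- **What the index needs.** Under Cognitive and Functional Assessment, "A Global Cognitive Index will combine z scores of all cognitive domains per established methods (8". The index therefore requires the cognitive battery.
- **When the battery is given.** In Table 1 the row headed "Neurocognitive Battery (Day 2" is marked at baseline, week 12 and week 24 only. The abstract says otherwise: "A comprehensive assessment of neurocognitive and functional performance and clinical symptomatology will be performed at baseline, mid-intervention (4 weeks, 8 weeks".

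**The concern.** The mediation analysis is the part of the plan that asks whether cognitive gain leads to functional gain. Its claim to temporal order rests wholly on measuring the mediator before the outcome. If the battery is not given at week 4 or 8, the mediator has no data behind it. The first post-baseline GCI would then fall at week 12, the same visit as the first post-baseline UPSA.

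Two things are at stake. An analyst who finds no mid-treatment GCI must choose a replacement, possibly after seeing data. One available replacement, GCI change to week 12 against week-12 UPSA, relates two measurements from the same visit and lacks the ordering that the text claims. In addition, readers cannot tell from the article how many times the two co-primary measures are collected.

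**Working it through.** The documents give no effect size or sample-size figure for this analysis, so the check compares the schedule with the analysis text.

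**Step 1: reproduce the visit totals in Table 1.** The inputs are the times printed beside each instrument and the row "Total Assessment Time (H:M". The formula is the sum of the times of the blocks or instruments marked at that visit.

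| Visit | Sum of what is marked | Result | Printed |
|---|---|---|---|
| Baseline | Clinical 2:30 + Functional 1:35 + Neurocognitive 2:15 | 6:20 | 6:20 |
| Week 4 | SIPS/SOPS 1:00 + AUS/DUS 0:15 | 1:15 | 1:15 |
| Week 8 | SIPS/SOPS 1:00 + AUS/DUS 0:15 | 1:15 | 1:15 |
| Week 12 | 2:30 + 1:35 + 2:15 + exit interview 0:30 | 6:50 | 6:50 |
| Week 24 | 2:30 + 1:35 + 2:15 | 6:20 | 6:20 |

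All five totals agree with the marks. The time left for cognitive tests at weeks 4 and 8 is 1:15 − 1:15 = 0:00.

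**Step 2: rule out a table-reading fault.** The battery heading, all 12 cognitive test rows and the Day 2 total show the same three marks. A lost cell would not repeat in every row and still leave the totals exact.

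**Step 3: ask what the totals would be if the battery were given mid-treatment.**

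- With the printed block time: 1:15 + 2:15 = 3:30.
- With the individual test times, which sum to 1:40 rather than 2:15: 1:15 + 1:40 = 2:55.
- With the printed block time and the UPSA (0:45): 3:30 + 0:45 = 4:15.

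None of these is 1:15. One coincidence should be set aside. The cognitive tests without the two WAIS subtests also sum to 1:15 (1:40 − 0:25). Those rows are not marked at weeks 4 and 8, however, and adding them to the two instruments that are marked would give 2:30.

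**Step 4: list the GCI changes that Table 1 allows.** These are baseline to week 12, baseline to week 24, and week 12 to week 24. None is mid-treatment. The UPSA, SLoF, SAS-SR and GAF are also marked only at baseline, week 12 and week 24. Week 24 is therefore the only functional visit that comes after a measured change in cognition.

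**Step 5: see what survives.** SIPS/SOPS is marked at all five visits. The plan also names symptom severity as a mediator, so a symptom change from baseline to week 4 or 8 can be computed and does precede the week-12 and week-24 outcomes.

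**The case against.** The strongest reply is that Table 1 may be the part that is wrong. The abstract places neurocognitive and functional assessment at weeks 4 and 8, and the mediation text presupposes it, so two passages stand against one table. Nor is the table free of error: its cognitive test times sum to 1:40 against a printed 2:15. This part of the objection stands. A reader might infer that none of the 120 projected participants will have the mediator. The documents do not support that as a fact; it follows only if Table 1 is correct. The reply does not remove the contradiction, because the itemised schedule and the analysis text cannot both be right.

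The second reply concerns importance. The plan says that mediators will be explored, and it describes the trial as a pilot meant to examine feasibility and generate effect sizes. A reader might infer that the efficacy comparison is compromised, or that all mediation work fails. Neither follows. If Table 1 is correct, the CCT versus RT comparison on the co-primary outcomes does not use a mid-treatment GCI, and symptom mediation remains possible.

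The third reply is that the planned logic is sound, since a mid-treatment mediator with a later outcome is properly ordered, and that nowhere do the authors propose a same-visit substitute. That is right. The same-visit analysis is a risk if the gap is left open, not something the plan intends.

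The inconsistency cannot be put down to an article condensing a fuller protocol. Both sides of it are printed in this document.

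**Conclusion.** The point holds as an internal contradiction with limited reach. On the schedule in Table 1, no GCI is measured between baseline and week 12. The exploratory cognitive mediation analysis therefore cannot be run as written, and its stated basis for temporal precedence is missing. The abstract contradicts that schedule.

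The conclusion rests on two assumptions: that mid-treatment means week 4 or 8, as the Assessments section says, and that Table 1 describes what is done. The exact agreement of all five visit totals makes Table 1 the more credible source, but does not settle the matter. If the abstract is right instead, the analysis can be run. Table 1 would then be wrong about two visits for both co-primary measures, which would also change the number of time points available to the main mixed model.

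This should be fixed before analysis. It does not put the trial's main comparison in doubt.

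**What to change.** Reconcile the abstract, Table 1 and the mediation text before the data are analysed, and state which is correct.

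**If Table 1 is correct:**

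- Correct the abstract so that weeks 4 and 8 cover only symptoms and substance use.
- Define the cognitive mediator as GCI change from baseline to week 12, with week-24 UPSA as the outcome, adjusted for baseline UPSA.
- Offer a version also adjusted for week-12 UPSA only as a sensitivity analysis. It removes functional gain already made by week 12 and so tests later change alone, which is a narrower question.
- Keep the mid-treatment mediator for SOPS symptom severity only.
- Label any association between week-12 cognition and week-12 function as concurrent, not as mediation.
- Reword the mediator-by-time terms, since a single outcome visit leaves no time factor in that model.

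**If the battery is in fact given at week 4 or 8:** correct Table 1 and its visit totals, and keep the mediator as defined. If the UPSA is also given then, as the abstract implies, mark it there too.

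Either route costs wording only and needs no new data. Under the first, cognitive mediation has one outcome visit, and loss to follow-up by week 24 lowers its power. The article gives no attrition figure from which to size that loss.
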